#### 4.5. Baseline

Baseline tests are:

1. Submaximal Chester Step Test
2. Anthropometry: Weight, Height, heart rate variability, blood pressure
3. \*Bloods for inflammatory markers as described above
4. Electromyography (EMG)
5. Health Related Quality of Life Questionnaire (IBD-Q)
6. HADS questionnaire
7. IBD-Fatigue Questionnaire
8. Faecal calprotectin (done as part of usual care at the NHS site, and only the result is used, no stool samples will be handled by the research team)
9. REDCAP participant 7 day input of pain perception and physical activity.

\*12ml of whole blood will be taken via venipuncture, by a team member training in phlebotomy who is on the delegation log. The blood will be centrifuged on site, the cellular component destroyed and discarded as per Health and Safety guidelines, the remaining acellular plasma will be stored in vials labelled with the participant pseudoanonymised number at -80 degrees centigrade, and then once all samples are collected from the study, they will be sent to [name] at The University of Central Lancashire by courier.

#### 4.6. Intervention(s)

The whole body vibration arm participants will have 18 visits to the University of Hertfordshire for their intervention (20 visits in total (+1 if they engage with the semi structured interviews). The WBV will involve performing static squatting on a synchronic vibrating platform. Patients will hold a squatting position with 30° of knee flexion, with their feet about 30cm apart, barefoot and with upper limbs holding the platform bars, for 60 seconds, then rest for 60 seconds, and repeat this a total of six times. The vibratory stimulus will be offered at an amplitude of 1.5mm with a frequency of 30 Hz.

During their visit, they will have 10 minutes of the lifestyle education programme, totaling 30 minutes per week.

Lifestyle education programme (30 minutes total):

- Week 1 - Healthy Eating Information from Crohn's and Colitis UK leaflets
- Week 2 - Discussing barriers and how to overcome them to Healthy Eating
- Week 3 - Physical Activity for IBD (Crohn's and Colitis video)
- Week 4 - Barriers to Physical Activity
- Week 5 - Overcoming barriers and positive steps forward to engage in Physical Activity.
- Week 6 - Smoking Cessation if applicable, round up of the last 5 weeks.

For the comparator arm - this programme will be delivered individually via zoom in one 30 minute session per week.

#### 4.7. Follow up Procedures

Any participants who exit the study prior to completion will be invited to feedback regarding the study.

The closing visit (if not undertaking the semi structured interviews) for the participant, will be a repeat of the baseline visit held at the University of Hertfordshire;

1. Submaximal Chester Step Test
2. Anthropometry: Weight, Height, heart rate variability, blood pressure
3. \*Bloods for inflammatory markers as described above
4. Electromyography (EMG)
5. Health Related Quality of Life Questionnaire (IBD-Q)
6. HADS questionnaire
7. IBD-Fatigue Questionnaire
8. Faecal calprotectin result (done at the NHS site where their Gastroenterology Consultant is, and only the result is used, no stool samples will be handled by the research team)
9. REDCAP participant 7-day input of pain perception and physical activity.

The first 15 participants to complete the intervention arm, who agree, will be invited to 1:1 semi-structured interview regarding the WBV exercise to gain more granularity regarding the experience, thoughts and feelings regarding WBV as an adjunct therapy for Crohn's disease.

\*12ml of whole blood will be taken via venipuncture, by a team member training in phlebotomy who is on the delegation log. The blood will be centrifuged on site, the cellular component destroyed and discarded as per Health and Safety guidelines, the remaining acellular plasma will be stored in vials labelled with the participant pseudoanonymised number at -80 degrees centigrade, and then once all samples are collected from the study, they will be sent to [name] at The University of Central Lancashire by courier.

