| Follow up duration | 
Data collection time points are visit 1 (pre starting WBV) , 6 weeks of WBV with data collection being EMGs, week 7 for bloods, stool, EMG and Questionnaires and week eight for the semi structured interviews. This will conclude the
                                                                                                                                                                                                                                                                                                                                                                                                                                                                                                                                                                                                                                                                                                                                                                                                                                                                                                                                                                                                                                                                                                                                                                                                                                                                                                                                                                          |

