### 5. Safety

Adverse event reporting will be conducted in accordance with the Sponsor's Adverse Event Reporting Procedures. A clinical co-investigator will be responsible for determining the causality and seriousness of adverse events, as well as all non-serious adverse events that are either deemed to be related to participation in the research or result in withdrawal from the WBV programme or study.

Serious adverse events are defined as any untoward medical occurrence that results in one of the following criteria: results in death; is life threatening; requires unplanned or prolonged hospitalization; results in persistent or significant disability or incapacity, or; results in a congenital abnormality or birth defect. Non-serious events are defined as any untoward medical occurrence that does not fulfil any of the serious adverse event criteria.

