## 6.3. Data Analysis

All analyses of the intervention-based data will be performed on an intention to treat basis.

To determine the effects of the intervention on all of the outcome measures, differences in the changes from baseline to after the 6 week intervention between the two groups will be examined using linear mixed effects models with group modelled as a fixed factor and random intercepts by participants adopted. For linear mixed models the mean difference between groups in change from baseline to after the 6 week intervention and 95% confidence intervals of the difference will be presented.

Effect sizes and their associated 95% confidence intervals will also be calculated for the changes from baseline to after the 6 weeks of intervention between the two groups, using Cohen's d, in accordance with McGough, & Faraone. Cohen's d values will be interpreted as 0.2 = small, 0.5 = medium, and 0.8 = large .

Analyses will be conducted in SPSS (IBM, SPSS, V28). The flow of participants through each stage of the trial will be presented in a CONSORT diagram. Descriptive statistics of means and standard deviations will be used to characterise the groups at baseline and differences between the two groups

will be presented in the form of an unadjusted mean difference for continuous outcomes, with their associated 95% confidence intervals.

In addition, Pearson chi-square tests of independence will be utilized to undertake bivariate crosstabulation comparisons between the two trial groups to test differences in the number lost to follow-up and the number of adverse outcomes in each group. Chi-squared probability values will be calculated using Monte Carlo simulation. All statistical analyses will be conducted using SPSS v28 (IBM, SPSS), with statistical significance accepted at the  $P \leq 0.05$  level.

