## 11. Data Protection and Participant Confidentiality

### Confidentiality

The Investigator has a responsibility to ensure that participant anonymity is protected and maintained. They must also ensure that their identities are protected from any unauthorised parties. Information with regards to study participants will be kept confidential and managed in accordance with the Data Protection Act, NHS Caldicott Guardian, The Research Governance Framework for Health and Social Care and Research Ethics Committee Approval.

Patient identifiable information shared across the research team is limited to name, email address and phone number. Hospital number and date of birth is collected on CRFs at the NHS site - but pseudo-anonymised with a patient research number. Only members of the research team will have access to this information.

The CI is custodian of the data.

The participants can withdraw at any stage, but any data collected up until the point of the withdrawal will still be used within the study. The patients will be asked for a preference of contact details and can withdraw this at anytime by informing the research team.

All data will be anonymised within any publications or dissemination of findings. The CI is the data controller and the research teams both on NHS site and at the University of Hertfordshire are the data handlers. The responsibility for data quality is described above. DPIAs will be completed for each NHS site with the University of Hertfordshire.

**Case Report Form (CRF)** forms are visit specific and are completed by the research assistant or member of the research team undertaking that particular visit parameter.

The Baseline and exit CRFs will record the data as described above

The WBV CRFs will confirm the number of WBV 60 seconds undertaken and confirmation of the lifestyle education delivery.

It will also confirm any AEs during the WBV intervention.

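### Section 4.7 does not secure the week-7 IBD-Q from participants who leave or stop early, so the data collected do not support the promised intention-to-treat analysis

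*Protocol*

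**What the plan says.** - **Early leavers.** Section 4.7 contains one sentence on them: "Any participants who exit the study prior to completion will be invited to feedback regarding the study". It then describes the closing visit at the university as a repeat of baseline, including the IBD-Q.
- **Timing.** The Trial/Study Summary places the questionnaires once after baseline: "week 7 for bloods, stool, EMG and Questionnaires". EMG is also listed during the six weeks; the IBD-Q is not.
- **Withdrawal.** Section 11 (Confidentiality) says that "any data collected up until the point of the withdrawal will still be used within the study".
- **Stopping versus leaving.** Section 5 refers to adverse events that "result in withdrawal from the WBV programme or study", so the protocol recognises two separate events. Section 4.7 does not mention the difference.
- **Analysis.** Section 6.3: "All analyses of the intervention-based data will be performed on an intention to treat basis". Change from baseline is compared using "linear mixed effects models with group modelled as a fixed factor and random intercepts by participants adopted".
- **Burden.** Section 4.6: "The whole body vibration arm participants will have 18 visits to the University of Hertfordshire for their intervention". For control: "For the comparator arm - this programme will be delivered individually via zoom in one 30 minute session per week".

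**The concern.** An intention-to-treat comparison needs the outcome from everyone randomised, including those who did not finish the programme. Here the primary outcome is measured once after baseline, in person, and the follow-up section asks early leavers for their opinion of the study but not for the IBD-Q. Staff following the text have no instruction to obtain the score from a person who is leaving. For a person who stops the programme but is content to stay in the study, they have no explicit instruction either way.

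The two arms are not equally exposed to this. WBV participants travel to campus 18 times for the intervention, while controls join six weekly video sessions. Section 1 names time constraints as a barrier to exercise, and pain, fatigue and toilet urgency as limits on activity in inflammatory bowel disease. Several of these reasons for stopping could also affect the IBD-Q. If loss is related to the outcome and differs by arm, the estimated effect can be distorted, and an uncollected score cannot be recovered later.

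**Working it through.** **1. What an early leaver contributes.** The IBD-Q is taken at baseline (Section 4.5) and at the closing visit (Section 4.7, week 7 in the Summary). A person who exits in between, and is asked only for feedback, has one IBD-Q value and no change score.

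**2. What the planned model does with that person.** Section 6.3 allows two readings.
- *Baseline and week 7 both modelled as responses.* The random intercept points this way, since it needs more than one record per person. Baseline-only participants stay in the model.
- *Change scores modelled by group.* Only group is named as a fixed factor, and the target is described as a difference in changes. Baseline-only participants drop out, and the analysis is of completers only.

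**3. The plan's own figures.** The protocol gives 168 participants (84 per arm) and a 16-point target, but no SD, power or loss rate. The allowance for loss therefore cannot be reproduced. For two-sided 5%, SD = 16 × √(n/2) / (z₀.₉₇₅ + z_power):
- 80% power, no loss (n = 84): 16 × 6.481 / 2.802 = 37.0. With 20% loss (n = 67): 33.1.
- 90% power, no loss: 32.0. With 20% loss: 28.6.

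The number 168 fits several combinations of SD, power and loss. This is context and not a separate criticism.

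**4. Size of the bias in a completers comparison.** Let q be the fraction lost in an arm, and g the amount by which the mean change of those lost falls below that of completers. The mean over all randomised in that arm is the completer mean minus q × g, so

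bias = q_WBV × g_WBV − q_control × g_control.

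Illustration (assumed): WBV completers gain 16 over control, those who stop gain 0, and control loss introduces no bias. The effect over all randomised is then 16 × (1 − q).

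| q in WBV arm | Effect, all randomised | Completer effect | Difference |
|---|---|---|---|
| 10% | 14.4 | 16 | 1.6 |
| 20% | 12.8 | 16 | 3.2 |
| 30% | 11.2 | 16 | 4.8 |

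The same formula shows the limits. With g = 16 in both arms and 10% lost in each, the bias is 0. With 25% against 10% it is 0.15 × 16 = 2.4. If those lost would have improved more than completers, g is negative and the sign can reverse.

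**5. Does the mixed model repair it?** This was simulated with 150 trials per mechanism and 84 per arm. Assumed inputs, none from the protocol: SD 30, baseline to week-7 correlation 0.5, true effect 16, and 25% missing in WBV against 10% in control. The mixed model used both time points as responses, with a time-by-group term.

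| Loss depends on | Complete data | Completers only | Mixed model |
|---|---|---|---|
| Nothing (at random) | 16.5 | 16.7 | 16.5 |
| Low baseline | 15.4 | 13.5 | 15.6 |
| Poor response | 16.3 | 20.7 | 19.8 |

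The Monte Carlo error of each average is about 0.4. The mixed model corrects loss explained by baseline. When loss follows poor response it is too high by 19.8 − 16.3 = 3.5 points, against 20.7 − 16.3 = 4.4 for completers only.

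**The case against.** The strongest reply is that the protocol is being read too harshly, on three counts.

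**Stopping is not exiting.** A reader might infer that anyone who stops WBV loses the outcome assessment. The text does not say so. The feedback sentence concerns people who leave the study, and the closing visit is not made conditional on attending WBV sessions. Section 4.8 ends the study once all participants have completed their scheduled assessments. Someone who stops WBV but stays enrolled may well be seen at week 7. This stands: for that group, loss is a risk left open by silence and not a stated rule. Keeping the data of people who withdraw consent only up to that point is also ordinary wording and not a fault.

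**Intention to treat does not necessarily become completers-only.** A reader might infer that it does. Section 6.3 does not support this as a fact, because on one of its two readings baseline-only participants are retained. Missing-data methods may also be in a statistical analysis plan that is not shown. This stands too, but those methods work on the data collected, and whom to follow up is fixed in Section 4.7.

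**The direction is not established.** A reader might infer that the result must favour WBV. That follows only if loss tracks poor response. In the table above, the completers-only bias is negligible under random loss and runs against WBV when loss depends on low baseline. The 16 × (1 − q) figures restate their own assumption.

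The protocol also requires ability to travel to all sessions, cites a tolerability pilot, and plans a chi-square comparison of numbers lost. These may reduce loss or describe it, but none of them obtains a missing score.

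**Conclusion.** The point holds as a gap between the follow-up procedure and the analysis promise. For those who exit early, the protocol as written provides no route to the single post-baseline IBD-Q. For those who only stop the programme, it does not say that they remain in follow-up. The intention-to-treat commitment is therefore not backed by data collection.

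The size cannot be fixed from the protocol, which gives no dropout rate. Under the one assumed mechanism in step 4, overstatement is 1.6 to 4.8 points for 10% to 30% stopping. Under the simulated poor-response mechanism it is about 3.5 points with the mixed model and 4.4 with completers only. Against a 16-point target that would be material. Under other mechanisms it could be nil or negative. Unequal loss is a reasonable inference from 18 extra campus visits, not a documented fact. The change is worth making because it is cheap and has to be made before the data are lost.

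**What to change.** Add to Section 4.7:
1. Stopping WBV or education is not withdrawal from follow-up.
2. Every randomised participant who has not withdrawn consent to data collection is offered the closing visit. At minimum, each is sent the week-7 IBD-Q, HADS, IBD-F and the seven-day diary through REDCap.
3. These values enter the primary analysis in the arm to which the participant was randomised.

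The existing feedback invitation can stay alongside this.

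Cost: REDCap links and reminders for those who stop or leave early. REDCap already handles e-consent and the pain and activity diary, so no new system is needed. The downside is that some questionnaires would be completed remotely instead of on site. Consent is respected, and no rule on the intervention itself changes.

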| Intervention       | 
After initial assessments (bloods for inflammatory markers, Chester step test, blood pressure, heart rate, faecal calprotectin, electromyograph of the thighs), participants will be randomly allocated to either a 6 week whole body vibration course and lifestyle education programme or a control group with lifestyle education. The whole body vibration means the participant is supervised crouching (static squat) on a vibration plate for 60 seconds at a time, 6 times, with 60 second rests in between, three times per week.
 
Both groups will get the lifestyle education programme which will equate to 30 minutes per week with two sessions on healthy eating, 3 sessions on physical activity and 1 round up or smoking cessation education. Both groups will undertake an electromyograph of their lower limbs (thigh muscles) at the beginning and end of the study. Both groups will undertake health related quality of life questionnaire (IBD-Q), HADS and IBD-Fatigue questionnaires, at the beginning and end of the study, as well as scoring their pain and level of physical activity daily one week prior and 1 week after the 6 weeks intervention, via REDCAP. The first 15 participants will be invited to participate in semi-structured interviews designed to gain feedback about how they felt the intervention went. Both groups will be asked to wear a chest strap and watch between the hours of 7am – 7pm, for three consecutive days following their first and last visit to the University of Hertfordshire. This is to assess heart rate variability.
 |

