| Comparison         | 
The comparator group will undertake the same as above, except without the WBV and the semi structured interviews.
                                                                                                                                                                                                                                                                                                                                                                                                                                                                                                                                                                                                                                                                                                                                                                                                                                                                                                                                                                                                                                                                                                                                                                                                                                                                                                                                                                                                                                                                                                |

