| Outcomes           | 
 
1. Change in health related quality of life indices (IBD-Q questionnaire)
 
2. Change in perceived fatigue (using questionnaire IBD-F) and muscle fatigue (using EMGs)
 
3. Static or improvement in pain perception
 
4. Measurement of disease activity with HBI, inflammatory markers in blood samples and faecal calprotectin
 
5. Qualitative markers of tolerability of WBV as a therapy.
 
6. Change in heart rate variability
 
                                                                                                                                                                                                                                                                                                                                                                                                                                                                                                                                                                                                                                                                                                                                                                                                                                                                                                                                                                                                                                                           |

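### The interviews, the only qualitative source specified for WBV tolerability, are limited in Section 4.7 to people who complete the WBV arm, while the Summary sets no such condition

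*Protocol*

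**What the plan says.** The Outcomes row of the Trial/Study Summary lists, as item 5, "Qualitative markers of tolerability of WBV as a therapy". It names no instrument. Section 2.1 has a related secondary end point on what patients think and feel about WBV as an adjunct treatment.

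The protocol describes who is interviewed in two places:

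- Summary, Intervention row: "The first 15 participants will be invited to participate in semi-structured interviews designed to gain feedback about how they felt the intervention went".
- Section 4.7: "The first 15 participants to complete the intervention arm, who agree, will be invited to 1:1 semi-structured interview".

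The Comparison row says that controls do the same "except without the WBV and the semi structured interviews", so both rules concern the WBV arm. The Follow up duration row sets "week eight for the semi structured interviews", after the six-week course and the week 7 assessments.

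For people who leave early, Section 4.7 says: "Any participants who exit the study prior to completion will be invited to feedback regarding the study".

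Other relevant data are collected. Section 5 has a clinical co-investigator assess adverse events that lead to withdrawal from WBV or from the study. Section 6.3 compares loss to follow-up and adverse outcomes between the arms and promises a CONSORT diagram. Section 11 says "The WBV CRFs will confirm the number of WBV 60 seconds undertaken" and that the same forms record adverse events during the intervention.

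**The concern.** For a tolerability question, completing the course is itself close to the thing being measured. Someone who stops because the sessions are painful, tiring or burdensome does not complete the arm and so, under Section 4.7, does not reach the interview. An account built only from completers will tend to favour WBV.

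The protocol presents the trial as the first study of WBV exercise as an adjunct in Crohn's disease, so a statement that patients found it tolerable may carry weight. The two sampling rules also differ on exactly this condition. Who is invited is a matter of trial conduct that an analysis plan would not normally settle. It also takes effect early, because the first 15 places are filled early in recruitment.

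**Working it through.** The protocol states no figure for this point that could be reproduced. The check compares the passages, followed by an illustration of size.

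**Step 1: does the tolerability outcome rest on the interviews?** Outcome 5 is qualitative and names no source. Section 4.7 describes the purpose of the interviews in nearly the same terms as the qualitative end point in Section 2.1. The interview is the only qualitative instrument with a stated sample, form and time point. The link is an inference, but a strong one.

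**Step 2: who can be interviewed?**

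| Source | Rule | Can someone who stopped WBV be interviewed? |
|---|---|---|
| Summary, Intervention row | First 15 participants | Yes, on its wording |
| Section 4.7 | First 15 to complete the WBV arm, who agree | No, on the natural reading |

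The two rules give different samples.

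**Step 3: do the other data fill the gap?**

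- *Exit feedback (Section 4.7).* It reaches early leavers in both arms, but it concerns the study in general, has no stated format or content, and is not tied to outcome 5. It is triggered by leaving the study, so someone who stops WBV but stays for the closing visit is not clearly covered.
- *Adverse events (Sections 5 and 11).* These capture events, including those that cause withdrawal. Someone may stop because of discomfort or burden with no reportable event.
- *Loss to follow-up (Section 6.3).* This counts people lost from the study. A person can stop WBV and still attend the closing visit.
- *Bout counts (Section 11).* These are recorded, but the protocol does not link them to tolerability.

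**Step 4: illustration of size.** From the protocol: 168 randomised 1:1, so 168 / 2 = 84 in the WBV arm. Scheduled bouts per person are 6 per session × 3 sessions per week × 6 weeks = 108. The interviews cover at most 15 / 84 = 17.9% of the arm.

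The protocol gives no stopping rate, so 10%, 20% and 30% are assumed, rounded to 8, 17 and 25 people of 84. If 15 are drawn at random from all 84, the expected number who stopped is 15 × K / 84. The chance of none is hypergeometric, C(84 − K, 15) / C(84, 15).

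| Assumed stoppers K of 84 | Expected among 15 | Chance of none among 15 | Under Section 4.7 |
|---|---|---|---|
| 8 (about 10%) | 15 × 8 / 84 = 1.4 | 19% | 0 |
| 17 (about 20%) | 15 × 17 / 84 = 3.0 | 2.3% | 0 |
| 25 (about 30%) | 15 × 25 / 84 = 4.5 | 0.3% | 0 |

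The last column assumes that a person who stops WBV does not count as completing the arm.

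**The case against.** A reader might infer that anyone who cannot tolerate WBV is excluded from the tolerability outcome by design, or that the trial will report tolerability only among those who tolerated it. The protocol does not support either statement. Outcome 5 never names the interviews as its sole source. Section 4.7 invites every early leaver to give feedback, with no cap of 15. Adverse events that lead to withdrawal are assessed, and loss to follow-up and adverse outcomes are compared by arm. The trial report as a whole will therefore carry information on people who did badly on WBV.

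Four further points are fair:

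- Stopping is not the same as intolerance. The course needs 18 intervention visits, and the Introduction names time as a barrier to exercise. Travel or a flare could also end participation. Conversely, someone can finish while tolerating WBV poorly and say so at interview.
- Completion is not defined, so the zero in the table depends on a natural but not certain reading.
- Fifteen qualitative interviews do not estimate a rate. The probabilities show how unlike the two samples are; they do not measure bias in any planned estimate.
- How adherence is summarised is commonly left to a statistical analysis plan, which is not at hand. The absence of a bout-count analysis is not itself an error.

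These points narrow the concern to the interview component. They do not remove it: the two sampling rules still conflict, and the stricter one still selects on a proxy for what the interviews are meant to describe.

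**Conclusion.** The point holds for the interview component. Under Section 4.7 the only specified qualitative source for tolerability is restricted to consenting completers of the WBV arm, and the Summary contradicts that restriction by omission. People who stop have only an unspecified feedback route that is not tied to the outcome. The direction of the selection favours WBV. Its size is unknown: at assumed stopping rates of 10% to 30%, roughly 1.4 to 4.5 of 15 interviewees taken without regard to completion would have stopped, against none under Section 4.7.

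The conclusion rests on two readings: that outcome 5 draws mainly on the interviews, and that someone who stops WBV has not completed the arm. The primary IBD-Q comparison and the other between-arm analyses are unaffected. This is a cheap improvement to a secondary, qualitative outcome.

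**What to change.** 1. Make the Summary and Section 4.7 state the same interview rule. Draw the 15 from those randomised to WBV whether or not they completed it, for example the first 15 who agree on reaching week 8 after allocation. Alternatively, reserve some of the 15 places for people who stop early.
2. Say how the exit feedback is collected and that, for the WBV arm, it contributes to outcome 5.
3. Alongside the interviews, report for everyone randomised to WBV the share of the 108 scheduled bouts completed and the number who stopped WBV, including those who stayed in the study. Give reasons for stopping with the counts, so that time, travel or a flare can be told apart from intolerance.

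The cost is protocol wording and one summary table. The number of interviews does not change and the bout counts are already on the WBV case report forms; reasons for stopping may need a field if they are not already recorded. The main drawback is that some people who stop will decline to be interviewed, so the sample may still lean towards those who tolerated WBV. The table for the whole arm limits the effect of that.
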